### Treatment in the intervention group: the Systematic Care Program for Dementia

The experimental intervention (training in the SCPD and its subsequent use) is based on the "family support model" as developed by Gruenberg [37] and Bengtson and Kuypers [17]. Its purpose is to strengthen the caregiver's competence and sense of competence. Basically, the SCPD consists of an assessment of the caregiver's sense of competence and depressive symptoms, and suggestions about how to deal with deficiencies. It can begin in the first consultation between a professional and a patient-caregiver dyad.

The SCPD can be divided into three stages:

1. *Screening*. Professionals screen the caregiver's sense of competence and depressive symptoms with the SCPD screening tool (inventory and interpretation) as presented in Figure 2. This means that professionals provide data about the Short Sense of Competence Questionnaire [38], depressive symptoms [39], and caregiver type [40]. They also provide their observations on the severity of dementia according to the *Diagnostic and statistical manual of mental disorders, 3^*rd *^text revision *(DSM-III-TR) [41].

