### The Systematic Care Program for Dementia

We have transformed the Family Support Program into a Systematic Care Program for Dementia (SCPD) that can be used in the first consultation of a professional with a patient and his/her informal caregiver (a patient-caregiver dyad) entering the health service. The SCPD consists of an assessment of the caregiver's sense of competence and suggestions on how to deal with competence deficiencies. The SCPD has been chosen because of its potential to help diagnose and treat problems systematically and to cover a wide range of individual problems. The SCPD is flexible in connecting pro-active interventions to individual problems. Moreover, it is also connected to the positive effects found in our previous study [18,35]. This program has been designed to fulfill the urgent need for effective and cost-effective support programs that can prevent overburdening the informal caregiver, which might result in a delay or decrease of patient institutionalization.

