### Eligibility criteria

Health services were considered eligible if they could enroll clients with suspected dementia or with dementia. Furthermore, they had to be sure that they could recruit enough patient-caregiver dyads.

Professionals recruited by the health services were considered eligible if they treated at least four of the patient-caregiver dyads each year (see the section *Power calculations*). This is the minimum number required for reasons of continuity and routine. Moreover, this minimum is necessary so that the intervention professionals can change their daily routine and become familiar with the SCPD method.

The eligibility criteria for the dyads were:

1. The patient was referred to and entering the health service with the suspicion of dementia.

2. The patient lives in the community.

3. The patient has an informal caregiver living in the community.

4. The informal caregiver visits the patient at least twice a week.

5. The informal caregiver is willing to participate and gives written informed consent.

The exclusion criteria were:

1. The patient has no informal caregiver.

2. The informal caregiver is a client of the health service her/himself.

3. The informal caregiver is seriously ill and unable to participate in the study.

4. The informal caregiver does not speak Dutch fluently.

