### Informed consent procedure

The informed consent procedure consisted of several steps. First, a psychologist or social psychiatric nurse provided written information for the informal caregiver. An informal caregiver who gave verbal consent and accepted the conditions was included in the next step. In this phase, the research assistant contacted the informal caregiver and made an appointment for the baseline interview, explained the assessment procedure, and answered questions. The informal caregiver was informed about the randomization procedure. After having given verbal consent, s/he received written confirmation of willingness to participate and the baseline questionnaire by post. An informal caregiver who was still willing to participate signed and returned the consent form and was included in the study.

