### Data collection at baseline and follow-up measurements

During the informed consent procedure, caregivers were asked to complete the baseline questionnaire. The research assistant and three trained interviewers collected baseline data and will collect follow-up data. If the caregiver cannot answer the questionnaire independently, assistance from the research assistant or the interviewer will be offered. Measurements take place at baseline (T_0_) and 3 (T_1_), 6 (T_2_), 9 (T_3_), and 12 months (T_4_) after inclusion. Table 1 presents the types of data to be collected at the various intervals. The completed questionnaires are to be returned to the IQ Healthcare, Radboud University Nijmegen Medical Centre, by post, and the research assistant will maintain caregiver anonymity while processing the data. The researcher and the research assistant are not involved in the assignment procedure, and they do not know the assignment decision. The blinding of the outcome assessor must remain intact until follow-up measurements are completed. The research assistant will process the professionals' data after follow-up measurements are completed.

**Table 1 T1:** Outcome measures

**Variable**	**PO**	**SO**	**EE**	**BG**	**Instrument/Source**	**T0**	**T1**	**T2**	**T3**	**T4**

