### Outcome parameters

Table 1 presents the types of data used for the outcome parameters:

1. The primary outcome measure is the institutionalizing of the person with dementia in a nursing home during the 12-month follow-up period. Both the institutionalization rate and the time to institutionalization will be taken into account. Possible institutionalization will be assessed every 3 months with one item of the Resource Utilization in Dementia questionnaire[42].

2. The secondary outcome measure is the quality of the caregiver's and the patient's lives. The quality of the caregiver's life will be measured with the Sense of Competence Questionnaire [35], the EuroQol-5D [43,44], the Center for Epidemiologic Studies Depression Scale [45,46], and the caregiver distress will be assessed with the Neuropsychiatric Inventory Questionnaire [47,48]. The patient's quality of life will be measured with the Neuropsychiatric Problems Inventory Questionnaire and the Quality of Life in Alzheimer's Disease [49,50].

Baseline variables as well as sociodemographic characteristics of both the patient and the informal caregiver are control variables. Sociodemographic characteristics are the severity of the patient's dementia according the DSM-III-TR [41], and the caregiver's relation to the patient and their living arrangements. The health service, gender, and job satisfaction [51,52] of the professional are also control variables.

Concerning the effect of the intervention on emotional functioning we expect positive changes on the secondary outcome quality of life – e.g. depressive symptoms, patients' problem behavior and caregiver distress as related to patients' problem behavior, sense of competence, and both caregiver and patient quality of life – at 12 months follow-up, in favor of caregivers and patients involved in the intervention group, as compared to controls.

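### SCPD may start at the first consultation, before the posted T0 questionnaire, so T0 scores used as control variables may already be affected in the intervention arm

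*Protocol article*

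**What the plan says.** All references are to the protocol article.

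- **Allocation.** Professionals were randomized before their dyads entered (Study design and setting), so a dyad's arm follows from the professional it is assigned to.
- **Start of SCPD.** The section describing the intervention says: "It can begin in the first consultation between a professional and a patient-caregiver dyad". The Background section on SCPD says that it "can be used in the first consultation of a professional with a patient and his/her informal caregiver", for dyads entering the health service. Its first stage screens sense of competence and depressive symptoms, and support follows.
- **Consent.** The Informed consent procedure opens: "First, a psychologist or social psychiatric nurse provided written information for the informal caregiver". The caregiver then consents verbally and is contacted by the research assistant. Next: "After having given verbal consent, s/he received written confirmation of willingness to participate and the baseline questionnaire by post". The last step is: "An informal caregiver who was still willing to participate signed and returned the consent form and was included in the study".
- **T0.** Data collection says: "During the informed consent procedure, caregivers were asked to complete the baseline questionnaire". Follow-up at 3, 6, 9 and 12 months is counted from inclusion.
- **Use of T0.** Outcome parameters says: "Baseline variables as well as sociodemographic characteristics of both the patient and the informal caregiver are control variables". Under Statistical analyses, the number of institutionalizations is tested with Fisher's exact test, time to institutionalization is described by Kaplan-Meier, and a Cox model corrects for control variables. Quality-of-life outcomes use random coefficient regression.

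**The concern.** A baseline score is a safe covariate only if allocation cannot have changed it. Here allocation is known to the professional from the outset, the programme may start at first contact, and T0 is completed at the end of a chain of steps that begins with a professional. A professional who follows the article as written may therefore screen and support a caregiver before that caregiver fills in T0. This can happen in one arm only.

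The scales at issue are the SCQ and CES-D, which measure what the SCPD screening tool addresses. The NPI-Q and EQ-5D are not screened, but the support stage could move them. If T0 already carries part of the effect, adjusting for it, or analysing change from it, removes that part from the estimate. The planned baseline comparison of outcome parameters could then no longer be read as purely pre-treatment.

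**Working it through.** **1. Order of events.** Put side by side, the sections give this sequence: professional randomized; first consultation, at which SCPD may begin; written information; verbal consent; research assistant's contact; questionnaire posted; signed form returned, which is inclusion. The article does not date the first consultation against the information step, and it does not say that SCPD was in fact delivered before T0. It sets no rule against this either.

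**2. The plan's own sample size.** The only planned figures nearby are 132 and 152 dyads per group. With 28% versus 14%, two-sided 0.05 and 80% power, using the pooled variance with mean 0.21:

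n = [1.960 × √(2 × 0.21 × 0.79) + 0.842 × √(0.28 × 0.72 + 0.14 × 0.86)]² / 0.14² ≈ 132.

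The design effect is 1 + (4 − 1) × 0.05 = 1.15, and 132 × 1.15 = 151.8, or 152. Both figures reproduce. They do not depend on this point; 132 is used below only as the effective number per arm.

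**3. Attenuation in a linear model.** Let D be the true 12-month effect, f the share of D already present at T0, and b the within-arm slope of outcome on T0. The arms then differ by f×D at T0, and the adjusted effect is

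D − b × (f × D) = D × (1 − b×f).

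The article gives neither b nor f, so the values below are assumptions. Power is for a continuous secondary outcome with 132 effective dyads per arm, residual SD √(1 − b²), and D set to give 80% power when f = 0.

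| b | f | share of effect kept | power |
|---|---|---|---|
| 0.5 | 0 | 1.00 | 80% |
| 0.5 | 0.10 | 0.95 | 76% |
| 0.5 | 0.25 | 0.875 | 69% |
| 0.5 | 0.50 | 0.75 | 56% |
| 0.7 | 0 | 1.00 | 80% |
| 0.7 | 0.10 | 0.93 | 74% |
| 0.7 | 0.25 | 0.825 | 64% |
| 0.7 | 0.50 | 0.65 | 45% |

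A pure change-from-baseline analysis corresponds to b = 1 and keeps 1 − f.

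**4. Which analyses are reached.** Fisher's exact test and Kaplan-Meier use no T0 scores, so this bias cannot enter them. The Cox model with control variables can be affected in the same direction, but the factor 1 − b×f is exact only for a linear model. Baseline-adjusted or change-based secondary analyses are affected as in the table. Characteristics such as age, gender and relation to the patient cannot be altered by SCPD.

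**The case against.** The strongest reply is that the wording is permissive. SCPD can begin at the first consultation; the article does not say that it did so before T0, and one screening contact may change little. A condensed article may also leave such sequencing to the full protocol. The first part stands: contamination of T0 is a possibility, and if nothing was delivered before T0 there is no bias. The second part does not remove the point. The article states both timings itself, and together they allow the overlap. It also presents early, systematic involvement of caregivers as the novelty of SCPD (Discussion, Strengths), so an early start is intended.

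A reader might also infer more than the article supports:

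- **That T0 is contaminated as a matter of fact.** No section says so.
- **That admissions before inclusion erode the planned 14-point difference.** With constant hazards of −ln(0.72)/12 = 0.0274 and −ln(0.86)/12 = 0.0126 per month, patients still at home at inclusion have 12-month risks of 1 − exp(−12 × 0.0274) = 28% and 1 − exp(−12 × 0.0126) = 14%. The difference stays 14 points however late inclusion falls. Community residence is an eligibility criterion in any case.
- **That the exclusion "The informal caregiver is a client of the health service her/himself" removes depressed caregivers from the intervention arm.** This needs screening, further assessment, treatment by the professional and client status, all before the form comes back. No section says that such care makes the caregiver a client, or that control professionals would not treat or refer caregivers.
- **That follow-up should be re-timed from the first consultation.** Every enrolled patient had to remain at home until inclusion, so moving the clock back among enrolled dyads adds immortal time. Patients admitted earlier were never enrolled and cannot be recovered.

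**Conclusion.** The point holds in a limited form. As written, the plan permits a T0 that follows SCPD exposure in one arm, and then makes baseline variables control variables without separating those that SCPD could have changed. If early SCPD contact moves T0 in the same direction as the final effect, the usual result is a pull toward zero. A T0-adjusted linear effect keeps 65% to 95% of its size for b = 0.5 to 0.7 and f = 0.10 to 0.50, and all of it if f = 0. In the same illustration, power for a secondary outcome falls from 80% to between 45% and 76%. These sizes rest wholly on assumed b and f. The test of institutionalization numbers and the Kaplan-Meier analysis are not in question; the adjusted Cox model and the secondary analyses that use T0 scores are.

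**What to change.** 1. Reconcile the two descriptions of when SCPD may begin with the Informed consent procedure and Data collection sections, so that T0 is measured before any SCPD exposure. How the steps are arranged to achieve this is for the sponsor.
2. Eligibility and consent are described in the past tense, so for dyads already enrolled the remedy is analytic. Flag those screened with SCPD before T0 where dates exist. The article does not say that the professionals' forms carry a date, so this may be possible for only some dyads.
3. Report the Cox and secondary models with an adjustment set limited to variables that allocation cannot affect (age, gender, relation to the patient, shared household), alongside the models that include T0 scores. State in advance that both will be shown.

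The cost is a wording change and one additional set of models, with some loss of precision where T0 scores are left out. If the dates show that T0 came first, the T0-adjusted models can be read as planned.

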**Figure 2 F2:**
[figure not shown]
**Screening tool for the Systematic Care Program for Dementia**.

2. *Psychosocial support*. The SCPD is flexible in connecting pro-active interventions to individual problems. Professionals use strategies aimed to support caregivers; for example, instructions on how to deal with the patient's behavioral problems. The clarification of the relation between the disease and the patient's problematic behavior is a SCPD support strategy. One goal might be that the caregiver will not take difficult behavior personally, which can diminish mutual negative feelings considerably. Professionals provide data about their support and interventions (actions) during and after each contact with the patient-caregiver dyad.

3. *Transfer to regular healthcare*. Along with psychosocial support, professionals might negotiate or organize respite care, which is like home care or day care. If the screening for caregiver depression gives cause for further screening for clinical depression, the professional may also refer the caregiver or start treatment. Professionals provide data about the organization and management of care if the case is transferred to other institutions or professionals.

### Training in the Systematic Care Program for Dementia

The training to teach professionals to use the SCPD consists of three sessions of 2 hours each. One meeting is for explaining the program, and two meetings are for the evaluation of the use of the program and for preparing suggestions on how to hand over the responsibility for care after the health service's work is completed. Figure 3 summarizes the objectives and methods used in the three training sessions. Several aids have been developed to facilitate the use of the SCPD:

**Figure 3 F3:**
[figure not shown]
**Training program for the Systematic Care Program for Dementia**.

1. *The SCPD screening tool*. The questions for the screening a caregiver's sense of competence and depressive symptoms are printed on a handy plasticized pocket card.

2. *The SCPD manual*. The manual consists of the items to be discussed during the training sessions (i.e., background information and methods), and some supporting literature has been added.

3. *The starter package and action list*. Several forms have been developed for the requested data. The starter package contains the forms that professionals need to gather these data. The action list contains 60 possible intervening and supportive actions that professionals might undertake as a result of the screening. They are divided into nine categories: intake, diagnostics, psychoeducation, psychosocial care, medical care, how to hand over care, legal care, case management, and crisis management. The list was developed in collaboration with a staff member and a social psychiatrist from each of the original three participating health services. Each person involved listed potential intervention and support actions. Repeatedly mentioned actions were included in the action list. Consensus for including actions on this list was reached.

### Treatment in the control group: usual ambulatory mental healthcare

Professionals randomized in the control group will continue their treatment for patient-caregiver dyads as usual. During the study period they will not receive the training in the SCPD. Usual ambulatory mental healthcare is characterized by late detection of caregiver problems and unsystematic support that differs among the health services [11-14].

### Data collection at baseline and follow-up measurements

During the informed consent procedure, caregivers were asked to complete the baseline questionnaire. The research assistant and three trained interviewers collected baseline data and will collect follow-up data. If the caregiver cannot answer the questionnaire independently, assistance from the research assistant or the interviewer will be offered. Measurements take place at baseline (T_0_) and 3 (T_1_), 6 (T_2_), 9 (T_3_), and 12 months (T_4_) after inclusion. Table 1 presents the types of data to be collected at the various intervals. The completed questionnaires are to be returned to the IQ Healthcare, Radboud University Nijmegen Medical Centre, by post, and the research assistant will maintain caregiver anonymity while processing the data. The researcher and the research assistant are not involved in the assignment procedure, and they do not know the assignment decision. The blinding of the outcome assessor must remain intact until follow-up measurements are completed. The research assistant will process the professionals' data after follow-up measurements are completed.

**Table 1 T1:** Outcome measures

**Variable**	**PO**	**SO**	**EE**	**BG**	**Instrument/Source**	**T0**	**T1**	**T2**	**T3**	**T4**

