**Methods and design:**

In our ongoing, cluster, randomized, single-blind, controlled trial, the participants in six mental health services in four regions of the Netherlands have been randomized per service. Professionals of the ambulatory mental health services (psychologists and social psychiatric nurses) have been randomly allocated to either the intervention group or the control group. The study population consists of community-dwelling people with dementia and their informal caregivers (patient-caregiver dyads) coming into the health service. The dyads have been clustered to the professionals. The primary outcome measure is the patient's admission to a nursing home or home for the elderly at 12 months of follow-up. This measure is the most important variable for estimating cost differences between the intervention group and the control group. The secondary outcome measure is the quality of the patient's and caregiver's lives.

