## Methods and design

### Study design and setting

The study design is a single-blind, multicentre, cluster, randomized, controlled trial. From September 2005 to February 2006, the research assistant enlisted and randomized professionals (psychologists and social psychiatric nurses), initially from four health services, either to the intervention group or the control group. One service dropped out because of the interference with another clinical trial. In order to enroll patients in due time three other mental health care services were included. Altogether, professionals from six health services and four regions were randomized to either the intervention group or the control group. This setback in recruiting patient-caregiver dyads prolonged the inclusion period by 4 months to a total of 17 months. The follow-up period has been set at 1 year. One year proved long enough for us to find significant effects in our previous study [36]. Figure 1 presents the flow of the participants through the trial at each randomization procedure.

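### The research assistant is said to have randomized the professionals and also to be unaware of assignment while collecting follow-up data, so assessor blinding is unsupported as written

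*Protocol article*

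**What the plan says.** Two sections of the protocol article describe the research assistant's part in allocation.

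- *Study design and setting*, on September 2005 to February 2006: "the research assistant enlisted and randomized professionals (psychologists and social psychiatric nurses), initially from four health services", to either the intervention or the control group.
- *Data collection at baseline and follow-up measurements*: "The researcher and the research assistant are not involved in the assignment procedure, and they do not know the assignment decision".

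The data collection section also gives this role outcome work: "The research assistant and three trained interviewers collected baseline data and will collect follow-up data". On help with the forms it says: "If the caregiver cannot answer the questionnaire independently, assistance from the research assistant or the interviewer will be offered". It then sets a firm requirement: "The blinding of the outcome assessor must remain intact until follow-up measurements are completed". It adds one safeguard: the research assistant processes the professionals' own data only once follow-up is over.

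Under *Informed consent procedure*, after the professional has handed over the written information, "the research assistant contacted the informal caregiver and made an appointment for the baseline interview". The abstract gives the link between the two levels of the design: "The dyads have been clustered to the professionals".

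**The concern.** Taken at face value, the two statements cannot both be true of one role: whoever randomized the professionals took part in the allocation and would ordinarily know its result. The data collection section states unawareness only for the researcher and the research assistant. It says nothing of the kind about the three interviewers. The one explicit statement that a data collector does not know the arm is therefore the one that another section contradicts.

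What is at stake is detection bias. Sense of competence (SCQ), depressive symptoms (CES-D), EQ-5D, NPI-Q and Qol-AD all rest on caregiver judgement. If the person helping a caregiver to answer knows the arm, that help can shift the answers. EQ-5D also supplies the QALYs, and RUD caregiving time supplies part of the costs, so the economic evaluation shares the exposure.

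**Working it through.** No figure in the plan bears on this point, so the check is a comparison of statements.

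1. **Who allocated.** *Study design and setting* names the research assistant as the one who randomized the professionals. No other section names a different role.

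2. **What was allocated.** The professional is the randomized unit and dyads are attached to professionals. Knowing a dyad's professional and that professional's group therefore gives the dyad's group.

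3. **What is denied.** The data collection section denies the research assistant both involvement in assignment and knowledge of it. There are two readings:
   - *Assignment means allocation to the trial arms.* This contradicts step 1 directly.
   - *Assignment means dyad to professional.* There is then no direct contradiction. But a research assistant who randomized the professionals can work out the arm as soon as the treating professional is known.

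4. **Is the treating professional hidden?** No such step is described. The research assistant approaches each caregiver after a professional has supplied the information. Under *Ethical principles*, the participant codes are open to the investigators and the research assistant. Neither fact proves that the research assistant learns which professional treats the dyad, but neither prevents it. Delaying the processing of professionals' data closes one route and does not remove knowledge gained by randomizing.

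5. **Where knowledge of the arm could act.** Table 1 and *Outcome parameters* give the follow-up measurements:

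| Measure | Follow-up times | Exposure if the helper knows the arm |
|---|---|---|
| SCQ, CES-D, EQ-5D, NPI-Q, Qol-AD | T4 | Higher: subjective ratings |
| RUD caregiving time | T1 to T4 | Higher: estimated by the caregiver |
| RUD residence item (primary outcome) | T1 to T4 | Lower: a fairly objective fact |

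6. **How many questionnaires.** Follow-up data are collected by 1 research assistant + 3 interviewers = 4 people. The article gives neither the share of questionnaires completed with help nor the research assistant's part of that share. The affected fraction is therefore unknown, and so is the size of any bias.

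**The case against.** The strongest defence is that the article has two steps: professionals are randomized to groups, and dyads are then assigned to professionals. The account of blinding under *Study design and setting* and the withdrawal rule under *Ethical principles* both use *assigned* for the second step. On that usage the denial need not conflict with the randomization statement. The usage is not uniform, however: *Statistical analyses* speaks of dyads being assigned to a group. The flow figure is not shown, and a condensed article may leave allocation mechanics to the full protocol. What stands is that the direct contradiction depends on the reading. The defence does not rescue the blinding claim, for the reasons in steps 3 and 4.

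Four stronger inferences are tempting, and the text does not support them.

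- *A reader might infer that outcomes were in fact assessed unblinded.* Inferring the arm requires knowing the treating professional, and the article does not say that the research assistant knows this.
- *A reader might infer that the single-blind label fails.* Dyads are declared blinded to their professional's group, and that is enough for the label. Assessor blinding is a separate claim.
- *A reader might count every questionnaire that the research assistant processes as affected.* Handling forms that a caregiver completed alone and posted cannot change the answers. The main route is help with completion, offered only to those who cannot answer unaided.
- *A reader might think only secondary outcomes are touched.* The research assistant also collects the RUD, which carries the primary outcome and the resource data, although the residence item is harder to sway.

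**Conclusion.** The point holds as a conflict between two sections that leaves the assessor-blinding claim without support as written. It does not show that any assessor was unblinded or that any result is biased. The size is unknown and cannot be derived from the article.

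The conclusion rests on two things: that the research assistant carried out the randomization, as *Study design and setting* says, and that nothing hid the treating professional from that role, since no such step is described. If either is wrong, a corrected sentence settles the matter. If both are right, assisted completion of the five scales at T4 and of RUD caregiving time at T1 to T4 is open to detection bias, while the institutionalization item is less exposed. The matter should be settled while the article still describes follow-up as ahead.

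**What to change.** First, reconcile *Study design and setting* with *Data collection at baseline and follow-up measurements*. State who carried out the allocation of professionals, who knew the result, what *assignment* means, and which data collectors were blinded. If the research assistant did not randomize, correcting the study design section is enough for that role, though the status of the three interviewers still needs a sentence.

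If the research assistant did randomize:

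- have the three existing interviewers give follow-up questionnaire assistance, kept unaware of both the allocation and the treating professional;
- record on each questionnaire who helped, if anyone;
- limit the assessor-blinding claim to the staff it is true of.

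Two other remedies would not repair the problem. A new holder of the allocation list cannot undo knowledge already gained, because the professionals have been randomized. A sensitivity analysis without the assisted questionnaires would drop a selected group, the caregivers who could not answer alone, so a changed estimate would not isolate assessor bias.

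The cost is a small reassignment of work among existing staff, one extra form field and a few corrected sentences.
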